### Data management and statistical analysis

Participants will receive a code upon entering the study. Coding will start at 001 and continue with +1. The signed consent form will contain the equivalence between the participant’s contact details and their code. All forms will be printed and stored in a locked drawer. The electronic forms will be stored in a protected space, which will be backed up regularly during the study. At the end of the study, the data will be stored in a repository, which guarantees that archiving and data sharing will be performed in accordance with FAIR principles. The study will be internally monitored.

The questionnaires (validated questionnaires, socio-demographic variables, satisfaction indices) will be implemented in the REDCap software [52], hosted at the HES-SO (University of Applied Sciences and Arts, Western Switzerland), which will be used to collect the data. The participant’s e-mail address will need to be entered in the platform to allow the surveys to be sent, but it will be coded as an identifier and not exported to the database. Only the participant’s code will represent the participant in the final database.

Missing data will be handled with a single imputation method. To test the hypothesis stipulating a pre-post difference between the participants of the two intervention groups and the participants of the control list, analyses of variance (ANCOVA analyses of covariance with time pre in covariate) will be conducted in order to compare the three groups BP, HW, and waiting list on the different dependent variables, with post-hoc analyses to compare the groups two by two. The primary outcome is body dissatisfaction assessed with the BSQ-8C. Similar analyses will be carried out for the secondary outcomes. Regarding the stability of the intervention and the hypothesis predicting that the observed effects will be maintained after one month of follow-up, repeated measures analyses of variance will be performed. The statistical analyses will be carried out with completers and intent-to-treat.

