### Random allocation

After receiving the consent form, the participant will be randomised into one of the three study arms, with a 1: 1: 1 allocation ratio. Randomisation will be blocked to ensure that groups are of equal size and that groups of six participants for each arm are regularly formed. The blocks will be of variable size (3, 6, 9) to protect the concealment. There is no stratification. The randomisation sequence will be implemented in the REDCap software, so none of the team members will know in advance which arm the next participant will be assigned to.

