### Sample size

To assess the effectiveness of each intervention, we will recruit a sample of 30 participants per arm, for a total N of 90 participants randomised into three groups. This sample size appears sufficient to detect a large pre-post effect on body dissatisfaction (primary outcome) according to data reported in previous studies [36], and including a hypothetical dropout rate of 10%. The effect sizes (Cohen’s d) reported in the Stice studies are large for the BP or the HW and generally exceed 0.50 (e.g. ref. [36] where the effect sizes were 0.90). To capture a pre-post effect of 0.50 with a power of 0.80 and a probability of 0.05, a sample of 27 people is needed for an intervention (calculated with G * Power 3.1 [37]).

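### Single imputation is fixed for missing data with no variant named, and each common variant tested harms the intent-to-treat ANCOVA: it either understates the standard error or shrinks the group difference

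*Protocol article*

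**What the plan says.** All references are to the protocol article.

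- **Missing data** (Data management and statistical analysis): "Missing data will be handled with a single imputation method". The section gives no variant, no correction of the variance and no sensitivity analysis.
- **Model** (same section): "analyses of variance (ANCOVA analyses of covariance with time pre in covariate) will be conducted in order to compare the three groups BP, HW, and" the waiting list, followed by two-by-two comparisons. "The primary outcome is body dissatisfaction assessed with the BSQ-8C".
- **Analysis sets** (same section): "The statistical analyses will be carried out with completers and intent-to-treat". Neither is called primary. The Blinding section mentions main analyses but does not tie them to one set.
- **Size and dropout** (Sample size): "we will recruit a sample of 30 participants per arm, for a total N of 90 participants randomised into three groups", "including a hypothetical dropout rate of 10" per cent. Allocation is equal (Random allocation): "with a 1: 1: 1 allocation ratio".
- **Source of missing outcomes** (Withdrawals): participants who develop an eating disorder or become pregnant leave the study after randomisation.

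**The concern.** A single imputation puts one value in each gap, and the ANCOVA then treats all 90 outcomes as measured. At 10% dropout only 81 are. If the filled-in values are built from the participant's own arm, they repeat the arm difference already seen in the observed data. They add no information, yet they lower the standard error. If the values ignore the arm, they are alike across arms and dilute any real difference.

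The hypothesis that both programmes improve body dissatisfaction compared with a waiting list rests on this ANCOVA. The risk is therefore an intent-to-treat result that is either too confident or too small, and the text does not say which. Because the completer analysis stands beside it unranked, the article does not say which result would carry the conclusion if they differ.

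**Working it through.** **Plan's own figure.** 27 / (1 - 0.10) = 30 per arm, so the planned dropout is 3 of 30 per arm, or 9 of 90. The 27 itself reproduces with a one-sided paired t-test (d = 0.50, power 0.812). A two-sided test needs 34. That is a separate matter and does not affect this point.

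**Inputs.** From the protocol: 30 per arm, three arms, ANCOVA on the pre score, 10% dropout. Assumed: pre-post correlation r = 0.5 (0.7 also run), outcome SD of 1, outcomes missing completely at random and equally by arm, and 20% dropout as a less favourable case. Pairwise tests are two-sided at 5%, without multiplicity adjustment.

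**Closed form, regression imputation using arm.** The estimate equals the completers' estimate, and the residual sum of squares does not change. The residual degrees of freedom go from 81 - 4 = 77 to 90 - 4 = 86, and the apparent n per arm goes from 27 to 30.

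- SE ratio (reported / true) = sqrt(77/86 x 27/30) = sqrt(0.806) = 0.90
- Actual type I error = 2[1 - Phi(1.96 x 0.898)] = 2[1 - Phi(1.760)] = 0.078
- At 20%: sqrt(68/86 x 24/30) = 0.795, and 2[1 - Phi(1.96 x 0.795)] = 0.119

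**Closed form, pooled imputation or baseline carried forward.** The imputed values have the same expectation in every arm, so the expected difference is (1 - dropout) x true difference. At 10%, 0.50 becomes 0.45 and 0.90 becomes 0.81.

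**Simulation, r = 0.5** (10,000 runs with no effect, 4,000 runs with a true difference of 0.50):

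| Method | SE ratio, 10% | Type I, 10% | Type I, 20% | Estimate of 0.50, 10% |
|---|---|---|---|---|
| Completers | 0.99 | 5.2% | 4.6% | 0.49 |
| Arm mean | 0.89 | 7.8% | 11.3% | 0.49 |
| Regression with arm | 0.89 | 7.8% | 11.5% | 0.49 |
| Stochastic with arm | 0.89 | 7.6% | 10.3% | 0.49 |
| Pooled mean | 0.99 | 5.1% | 4.6% | 0.44 |
| Pooled regression | 0.99 | 5.1% | 4.6% | 0.44 |
| Pooled stochastic | 0.99 | 5.0% | 4.6% | 0.44 |
| Baseline carried forward | 0.99 | 4.9% | 4.5% | 0.44 |

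The shrinkage relative to completers is 0.44 / 0.49 = 0.90, as the formula predicts. A true difference of 0.90 was estimated at about 0.81 by the pooled methods and carry-forward. With r = 0.7 the arm-specific error rates were 7.6% to 7.8% at 10% dropout and 10.7% to 12.4% at 20%. Across repeated runs the ranges were about 7% to 8% and about 10% to 13%. The three-arm F test at 10% dropout rejected in about 8% to 9% of runs.

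**Unequal dropout under carry-forward.** Assume a fall of 0.4 SD common to all arms, no treatment effect, and loss of 6 of 30 in each intervention arm against 1 of 30 on the waiting list. The expected false difference is 0.4 x (6/30 - 1/30) = 0.067 SD, and the simulation gave 0.068. Here it counts against the interventions. It would favour them if the waiting list lost more.

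**The case against.** A reader might infer that any single imputation inflates the false-positive rate. The protocol does not support that. It names no variant and does not say whether imputation is within arm or pooled, and four of the seven variants tested keep the type I error near 5%. With balanced dropout those four err towards no difference. This objection stands, and it limits the claim of a too-small standard error to arm-specific imputation. It does not clear the plan, because those four pay for their nominal error rate with a diluted effect.

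The document is also a journal article. The imputation model, and whether it applies to items or to whole assessments, may be set out in an analysis plan that is not shown. That is fair for the detail. The class of method, however, is stated, and a plan that follows it can only choose among single imputations.

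A reader might also infer that two unranked analyses allow the favourable one to be headlined. The text goes only as far as listing both. A separate plan could rank them, and the main analyses go to a statistician blinded to allocation. The completer ANCOVA also holds its error rate under the completely-at-random assumption, so it gives a partial check. The missing ranking is therefore a lesser point.

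Finally, the trial is described as preliminary and aimed at large effects. At 10% dropout the distortion is unlikely to overturn a large effect. That stands too, and it bears on severity.

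**Conclusion.** The point holds in a conditional form. The protocol commits to single imputation, and every common variant tested harms the intent-to-treat ANCOVA in one of two ways:

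- **Arm-specific variants:** the standard error is about 10% too small, and the pairwise type I error is about 7% to 8% instead of 5%.
- **Pooled variants and baseline carried forward:** the type I error stays near 5%, but a true difference loses about 10% of its size. Carry-forward adds bias if dropout differs by arm.

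These sizes rest on the protocol's 10% dropout, data missing completely at random and an assumed correlation of 0.5; 0.7 changes little. The 10% to 13% error rate needs an assumed 20% dropout. Withdrawal for an emerging eating disorder is plausibly related to the outcome. Missingness may then not be completely at random, and neither single imputation nor the completer analysis addresses that. Severity is moderate.

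**What to change.** Replace the single-imputation sentence with one of the following:

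- **Multiple imputation**, with arm, T0 scores and the other collected scales in the imputation model, and results combined so that the imputation uncertainty enters the standard error.
- **A likelihood-based mixed model** of the BSQ-8C at T1 and T2, adjusted for T0, with separate arm effects at each time because the waiting list receives the BP before T2. To keep participants who have no later assessment in the model, T0 can be entered as an outcome with a mean common to all arms.

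State that the intent-to-treat analysis of the BSQ-8C at T1, with all randomised participants in their allocated arms, is primary and that the completer analysis is supportive. Add a sensitivity analysis for outcomes that are not missing at random.

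Recruitment, sample size and assessments do not change. The cost is a little more programming and, compared with arm-specific single imputation, slightly wider confidence intervals. The change should be recorded before the outcome data are analysed.

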### Ethics

The study was approved by the Ethics Committee of Geneva, Switzerland (project ID 2020–01010, version 3.0 approved on July 14^th^, 2020) and is registered in the Swiss National Clinical Trial Portal (SNCTP000003978), as well as in ClinicalTrials.gov (NCT04558073). Participants will receive a detailed information sheet by mail explaining the study goals, procedures, and potential risks and benefits. They will be informed that participation in the study is voluntary and that they can withdraw at any time without impacting the course of their university studies. After they have had sufficient time to review this information, they will sign a written consent form, which they will mail back to the study investigators. This consent will be obtained before any procedure is initiated. There is no financial compensation for participating in this study. One month after the last assessment, all participants will be proposed an individual debriefing session via videoconference, in order to close their participation and ensure they do not need any referral to a consultation centre.

## Discussion

This study will provide initial results on the acceptability and effectiveness of the BP and HW interventions in French-speaking Switzerland. These results will be disseminated through scientific articles and at conferences on eating disorders and body image. In order to disseminate the results in the community, we will communicate them to the two main French-speaking websites dedicated to adolescents and young adults health promotion. Potential cultural adaptations that might emerge from the participants’ comments will be considered and discussed with the designers of the interventions, before being adopted. We do not expect major adaptations, since at least the BP programme was used successfully in other cultures than the US without fundamental change [25,26]. In addition, these preliminary data will be used as a basis to write a grant proposal for national funding agencies for investigating the mediating or moderating factors involved in the prevention of eating disorders. In particular, the mechanisms at play in the HW are not yet well understood [53]. An analysis of the stability of the effects of interventions, as well as their effect on the development of eating disorders, requires a larger sample and a longer follow-up period.

## Conclusion

This study is a first step into the field of selected prevention of eating disorders in Switzerland, where eating disorders are highly present and evidence-based prevention interventions are still lacking.
